#### Concealment mechanism {16b}

Only the person that has generated the list has access to it.

#### Implementation {16c}

The eligible patient will be randomized, with a 1:1 allocation, via an internet server (access by secure code 24/24; RedCap) in one of two groups: SinnoTest group or control group. A blood sample will be extracted from the patient randomized in the software arm for the determination of selected biomarkers for the use of SinnoTest®. A patient randomized to the control arm will also have his/her blood drawn (but this one will not be analyzed) so that the two arms are identical and to maintain blinding for the patient.

The coordinating center will manage its development and its availability on the internet. It will only be done after informing the patient and signing the consent. The randomization will be individual with blocks of random size, stratified by center. The investigator or CRA will connect to the server after confirming that the patient meets all the inclusion/exclusion criteria. Block randomization will ensure that an equal number of patients are randomized to each study arm and to each study site.

The involvement of 5 centers in this study allows individual randomization without fear of the existence of a contamination bias. Indeed, investigators may change their empirical management under study because of patient outcomes previously included with SinnoTest®, but the relatively low inclusion counts per center suggest that this bias will be negligible. In addition, in the control arm, the treatments will be prescribed by the rheumatologist who usually treats the patient, so the number of patients who will have the opportunity to “learn” is even lower, because it is shared among all doctors that include patients in the study.

This design also neutralizes the disappointment bias of investigators who can all use the innovation under study. By stratifying by center, about half the patients will have their treatment prescribed by SinnoTest, so they can be sure they will have the opportunity to use the software and assess its functions.

### Assignment of interventions: blinding

#### Who will be blinded {17a}

Study subjects will be blinded to the intervention (who decides the medication prescribed). Evaluators will also be blinded to the intervention where the subject was allocated.

#### Procedure for unblinding if needed {17b}

This is a single-blind study (single blind). Only the doctor knows the details of how to prescribe treatment (i.e., the doctor knows if the patient is in the control group or the group using the SinnoTest® software). Lifting of the blind is not applicable.

The investigator carrying out the aleatorization will be responsible for the blinding of the subject.

### Data collection and management

#### Plans for assessment and collection of outcomes {18a}

The use of the SinnoTest® V1 device is reserved for hospital rheumatologists. Training in the use of the graphical interface will be dispensed. In addition, manuals have been created for the use of the device and for the collection, processing, and delivery of samples.

#### Plans to promote participant retention and complete follow-up {18b}

In order to maximize the retention rate of the subjects included in the study, several strategies will be put in place:
Participants will be asked to provide both phone and email addresses, as well as the best time to contact them.Study subjects will also be educated in the significance of research follow-up even if they decide to discontinue the study drugs. Explaining how their experiences with the treatments, whether positive or negative, are critical to evaluating the intervention under study can increase their understanding of the research process and lay the groundwork for future discussions about the importance of completing research assessments.Anticipated barriers to attending appointments such as transportation, work schedules, vacations, and childcare can be reviewed up front and resolved.Phone calls regarding study visit reminders will be used for all appointments, and rapid follow-up of missed appointments will be incorporated into the protocol.The schedule of study visits will be flexible, ensuring subject retention.

### Data management {19}

Electronics case report forms (eCRFs) will be used that comply with the general and specific good practice standards, as well as the highest requirements for computer validation, with restricted access at the user level, provided with inconsistency detection filters and with traceability of all the information until the final closing of the study. CRFs must be completed for each subject screened/enrolled in this study. This also applies to patients who do not complete the full follow-up planned in the trial.

All CRFs must be filled out by the personnel duly authorized to do so, who will have access codes to the application for entering personal and non-transferable data. The investigator will keep the records and data during the trial in compliance with all legal and regulatory provisions in force. All data must be supported by original documents in the test center. Any record or document used as a source of information (which will be called the “original data of the subject”) will be kept for review by authorized representatives of the promoter or regulatory bodies. The CRFs will be filled in as soon as possible after the evaluation has been carried out.

All the dates that appear in the CRFs referring to analytical tests and other data must coincide with the dates in which the samples were obtained or the procedures were performed.

#### Study database

To facilitate the statistical analysis, a computerized database will be created in which the integrity of the data from the CRFs will be recorded, so that an exact replica of the information contained in them is created.

A data management plan will be made before the beginning of the definition of the database in which the recording process and the errors and consistency controls that will be performed on the recorded data will be detailed. A dictionary of variables will be generated in which the correspondence between the data contained in the CRFs and the variables of the database will be detailed, as well as the codifications used and the meaning of the recorded values.

In the event of inconsistencies or errors in the data, requests for clarification will be generated for the researchers for their verification or correction, which will be treated in an equivalent way to the CRFs. Access to the database will be restricted to the Data Manager (design, input, and data cleansing) and the personnel in charge of data transcription (data entry).

Prior to the declaration of the definitive database, a verification is done of the consistency of the values of the inclusion/exclusion criteria, of the clinical evaluations, of the results of complementary explorations, of the dates of the visit, of the compliance, of the medication received, of the adverse events, of the information about dropouts, and of the evaluation of effectiveness.

A definitive database will be declared that will be registered with signature and date. Two protected copies of the same will be kept, and paper lists of the variables contained in the database will be generated for archiving. The final database will be used for statistical analysis.

#### Registry and file maintenance

All the essential documentation of the clinical trial will be filed in a master file of the study, whose safe and complete conservation will be ensured for the time required according to the legislation in force and at the disposal of the authority that requests it. This documentation will include the following: work protocol (final version) and amendments; models of all the employed versions of information sheet and informed consent form; CREC permits; authorizations of the health authorities; curriculum vitae of all the personnel participating in the study; random assignment list and treatment allocation codes; individual data collection notebooks; documentation related to the study monitoring procedures; documentation of the study database and definitive database; documentation of data management and clarification requests; statistical analysis; adverse event notifications; final report; certificates of audits; standardized work procedures applied in the study; study financing and payments; correspondence.

### Confidentiality {27}

The investigator will ensure the right to privacy of patients and must protect their identity against unauthorized third parties. The study monitor may have access to the patient’s identity and data in relation to the study’s monitoring procedures.

The investigator will keep a patient identification list updated with the correspondence between the name, clinical history number, and the patient’s identification number or code for the clinical trial, which will be kept together with the patients’ informed consent forms in a file unique in the center. The full name of the patient should not appear in any other section of the data collection notebooks or study documentation. At the end of the study, a copy of the list in which the names of the patients will be hidden will be included in the file of the researcher of the study.

In case that an audit of the study is conducted, the auditors who perform it, as well as the health authorities that may require it for regulatory purposes related to the study, may also have access to patient data.

All participants in this research project expressly commit themselves not to disclose the identity of the treated patients and to respect the rules of confidentiality regarding the data and information to which they have access when participating in the trial. The personal data collected and stored for the purpose of this study will be treated in accordance with the provisions of the General Data Protection Regulation (GPDR: Regulation EU 2016/679).

### Plans for collection, laboratory evaluation, and storage of biological specimens for genetic or molecular analysis in this trial/future use {33}

In the case a subject agrees to participate in the proteomics substudy, after carrying out the planned experiments during the trial, the remaining biological samples will be donated to the biobanks belonging to the corresponding ISCIII Biobank Network of each participating center and the Biobank of the Center Hospitalier Universitaire Grenoble Alpes (France). These samples may be transferred to other researchers, in accordance with current regulations (Biomedical Research Law 14/2007 and Royal Decree 1716/2011), to carry out studies related to their disease. Any project for which samples are used will be previously approved by an accredited Ethics Committee.

### Statistical methods

#### Statistical methods for primary and secondary outcomes {20a}

##### Description of the population studied

The study population will be described by a flow diagram according to the CONSORT recommendations (CONsolidated Standards Of Reporting Trials). The different variables (demographic and biological) will be described by treatment arm: for quantitative variables, number of data analyzed, mean, and standard deviation, Q1, Q3, minimum, maximum, and median, and for qualitative variables, number of analyzed data, absolute frequencies, and percentage.

#### Primary outcome measures

##### *Clinical primary outcome measures*

Therapeutic response

Therapeutic response at 6 months will be described using number of analyzed data, absolute frequencies, and percentage.

Comparison between the study arms will be performed using logistic regression models. Models will be adjusted by baseline variables, and they will allow us to estimate an effect size for the difference between study arms regarding the clinical variables.

#### Secondary outcome measures

##### *Clinical secondary outcome measures*

Disease activity, quality of life and disability

Clinical parameters at 6 months will be described using number of analyzed data, mean, standard deviation, Q1, Q3, minimum, maximum, and median, for DAS28-ESR, DAS28-CRP, EQ5D-5L, and HAQ.

Comparison between the study arms will be performed using linear regression models. All models will be adjusted by baseline variables, which will allow us to estimate an effect size for the difference between study arms regarding the clinical variables.

In addition, as disease activity, quality of life, and disability will be assessed at baseline, 3 months, and 6 months, their evolution will be analyzed using generalized estimating equations models nested by patient [26, 27] and adjusted by study visit and study arm, using a Gaussian family and Identity as link function. Different covariable structures will be tested (independent and exchangeable) and compared using the Quasi-Akaike Information Criterion [28]. Time × study arm interactions will assess different effects of time in the evolution of DAS28-ESR, DAS28-CRP, EQ5D-5L, and HAQ by study arm. A *p* value < 0.05 will be considered as a significant interaction. For each outcome, in case the interaction is not significant, we will consider that there is no statistically significant difference in the evolution of that outcome between study arms.

Software’s predictive model performance

Sensitivity, specificity, and positive and negative predictive values, and likelihood ratio will be described. The performance of the SinnoTest® will be calculated in the “SinnoTest®” arm by comparing the response predicted by the software and the response observed at 6 months. It will be analyzed globally and for each of the biotherapies.

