### Sample size {14}

To re-evaluate the metrological properties of SinnoTest®, including 90 patients per group will highlight a differential response rate between the software arm and the control arm of more than 18.2%, considering a current response rate of 65% (defined as an EULAR good response [24]) with conventional care (control arm). The number of subjects required was estimated considering a bilateral alpha risk at 5% and a power of 80%. In total, 180 patients will be the estimated number of participants needed to achieve study objectives.

Due to the subject’s and the study’s characteristics, no allowance for loss to follow-up was considered in the sample size calculation: patients with a chronic disease, probably being followed up in the same center and by the same rheumatologist for some time (> 1 year), and the short follow-up time for the primary outcome.

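### The GEE for DAS28, EQ-5D-5L and HAQ treats the randomised baseline as an outcome and judges the arms by an interaction p value alone, which loses power that a baseline covariate would recover at no cost (minor, secondary outcomes only)

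*Protocol article*

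**What the plan says.** Under Statistical methods {20a}, Clinical secondary outcome measures, the protocol article plans two analyses for DAS28-ESR, DAS28-CRP, EQ-5D-5L and HAQ.

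- **Month-6 regression.** "Comparison between the study arms will be performed using linear regression models. All models will be adjusted by baseline variables". It is meant to yield an effect size for the arm difference.
- **GEE over time.** This is introduced as an addition. It uses the baseline, month-3 and month-6 assessments, nested by patient, with visit and arm as terms, a Gaussian family and identity link. Independent and exchangeable working correlations are to be compared. The time × arm interaction is tested at 0.05, with this rule for each: "in case the interaction is not significant, we will consider that there is no statistically significant difference in the evolution of that outcome between study" [groups].

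The Sample size section {14} addresses only the response rate: "including 90 patients per group will highlight a differential response rate between the software arm and the control arm of more than 18.2"%. Neither section gives an SD, a within-patient correlation or a target difference for the four continuous outcomes.

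**The concern.** In a randomised trial the arms have the same expected baseline mean. A model that gives each arm its own baseline mean, and then asks whether the arms move differently from it, estimates something the design already fixes. Chance imbalance at baseline passes in full into each change score, and the interaction pays for it in variance. Using baseline as a covariate removes only the part of the imbalance that predicts the later value.

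The only verdict sentence written for these outcomes is tied to this test and rests on its p value, with no estimate or interval. It can therefore report a non-significant evolution while the month-6 regression on the same data shows a difference, and the protocol does not say how the two would then be read together. Four secondary outcomes are affected, including quality of life and disability. The primary response analysis is not, and neither are the QALYs, which have their own area-under-the-curve calculation and comparison.

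**Working it through.** **The plan's own figure.** Inputs from Sample size {14}: 65% against 65 + 18.2 = 83.2%, two-sided 5%, 80% power. Pooled-variance formula, mean proportion 0.741:

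n = [1.960·√(2·0.741·0.259) + 0.842·√(0.65·0.35 + 0.832·0.168)]² / 0.182² = (1.214 + 0.510)² / 0.0331 = 89.8, so 90 per arm. Power at 90 is 80.1%. The figure reproduces, but it says nothing about the continuous outcomes.

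**Inputs for the comparison.** From the documents: n = 90 per arm, 1:1 allocation, two-sided 0.05. Assumed: SD 1 at every visit, exchangeable correlation r = 0.3 to 0.7, month-6 difference d in SD units, month-3 difference f·d, complete data, visit as a factor.

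**Variance of one contrast** (times 2/n):
- difference in change scores: 2(1 − r)
- difference adjusted for baseline: 1 − r²
- the gap is 2(1 − r) − (1 − r)(1 + r) = (1 − r)², which is never negative.

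**Noncentrality of the 2-df test on the month-3 and month-6 contrasts:**
- baseline as outcome (time × arm interaction): λ = n·d²·(f² − f + 1) / [3(1 − r)]
- baseline as covariate (joint arm effect at both visits): λ = n·d²·[(1 + r)(f² + 1) − 2rf] / [2(1 − r)(1 + 2r)]

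Power is the probability that a noncentral chi-square with 2 df exceeds 5.991.

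**Worked case**, d = 0.3, r = 0.5, f = 1, so n·d² = 8.1:
- as outcome: 8.1 × 1 / 1.5 = 5.40, power 54%
- as covariate: 8.1 × 2 / 2 = 8.10, power 72%

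**Results at d = 0.3:**

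| r | f | Baseline as outcome | Baseline as covariate |
|---|---|---|---|
| 0.3 | 0.5 | 31% | 49% |
| 0.3 | 1.0 | 40% | 67% |
| 0.5 | 0.5 | 42% | 55% |
| 0.5 | 1.0 | 54% | 72% |
| 0.7 | 0.5 | 64% | 72% |
| 0.7 | 1.0 | 77% | 86% |

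If the effect wanes after month 3 (f = 1.5, r = 0.5), the powers are 79% and 92%, so the order is the same.

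**Other effect sizes**, same r, f = 0.5 or 1: at 0.2 SD, 16–42% against 24–50%; at 0.4 SD, 52–96% against 75–99%.

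**Time coded linearly.** With three equally spaced visits, the slope contrast uses only month 6 minus baseline. Power at d = 0.3 is then 40%, 52% and 74% for r = 0.3, 0.5 and 0.7. The month-6 regression adjusted for the baseline value has 56%, 64% and 80%. The loss does not depend on the 2-df coding.

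**Where the loss is small.** If the planned response gain is read as a shift on a normal scale (an assumption), it is probit(0.832) − probit(0.65) = 0.58 SD. The interaction test then has 84% to over 99% power, so little is left to gain on DAS28 if the planned effect is real.

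**The case against.** The strongest defence is that the plan draws no wrong conclusion. A reader might infer that a non-significant interaction is taken as proof that the arms do not differ. The text does not support that: it says only that no statistically significant difference in evolution was found, which restates the test result. A reader might also infer that the interaction overrides the month-6 comparison. It does not: the regression is stated first, stands on its own, and the GEE is an addition. Both points stand.

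It is also tempting to say that the test misses modest differences in most trials. That is not general. Under the assumptions above the miss rate is 23–69% at 0.3 SD and 4–48% at 0.4 SD, and exceeds half throughout only at about 0.2 SD or less. There the month-6 regression is weak too (29–47% power), which reflects the size of the trial.

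Nor is the interaction always weaker than the month-6 regression. With visit as a factor and a month-3 effect 1.5 times the month-6 effect, it has 79% against 64% at 0.3 SD and r = 0.5. That stands against a claim about the month-6 regression. It does not touch the comparison here, because moving baseline to the covariate side raises the power of the same two-visit test in that case as well.

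Finally, a time × arm interaction in a GEE that includes baseline is valid and conventional, and relevance margins and exact covariate lists can be left to an analysis plan. The point is one of efficiency, not validity.

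**Conclusion.** The concern holds as a minor one, confined to the four continuous secondary outcomes. As the text is naturally read, the GEE puts the randomised baseline among the outcomes and so tests differences in change scores. This is never more precise than adjusting for baseline.

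At 90 per arm and 0.3 SD, with r from 0.3 to 0.7 and a month-3 effect half of or equal to the month-6 effect, power is 31–77% as written and 49–86% with baseline as covariate. The gain is 8 to 27 percentage points, largest at low correlation. It rests on an assumed SD, correlation, effect size and month-3 pattern, on complete data and on visit coded as a factor; the protocol gives none of the numerical values. The direction of the gain does not depend on them.

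The documents do not support a charge of accepting the null, of an equivalence claim, or of a rule that displaces the month-6 regression.

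**What to change.** 1. In the GEE, use months 3 and 6 as outcomes and the outcome's own baseline value as a covariate. Judge the arms by the arm contrast at each visit, or the joint test of both. Once baseline is a covariate, the remaining arm × visit term asks only whether the month-3 and month-6 effects differ, so it should not carry the verdict.
2. Alternatively, keep all three visits as outcomes and constrain the baseline means to be equal across arms. This needs a working correlation other than independence, since under independence the baseline values add nothing to the later contrasts.
3. Replace the p-only sentence with the arm difference at each visit and its 95% CI.
4. Keep the month-6 regression as the arm comparison and state that its baseline variables include the outcome's own baseline value.

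This costs a few sentences in the statistical section and the analysis plan. The baseline, month-3 and month-6 values are already scheduled, so no patients, visits or data are added.
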